### Allocation concealment

Each study site will receive a block of sequentially numbered, sealed, and opaque envelopes containing treatment allocation for either ‘SLT’ or ‘Drops’. Opaque envelopes will be opened in order of sequence per site. A unique study code will be assigned to each patient at randomisation, consisting of a three-digit randomisation number along with the patient’s initials.

### Outcome measures

#### Health-related QoL (HRQOL)

Considering (a) the substantial side effects of topical medication(s) and poor adherence and (b) its considerable impact on daily living and QoL, HRQoL parameters are our critical outcomes to determine the treatment of choice for glaucoma. The *primary patient-centred outcome* will be assessed by significant changes in two glaucoma-specific scales and one generic HRQoL instrument at 6 weeks and at 6, 12, and 24 months post-treatment. These tools include the following:*Glaucoma Outcome Assessment Tool (GOAT):* We have developed a glaucoma-specific QoL item bank, GOAT, which contains 342 items across 10 specific QoL domains [36]. An item bank is a pool of calibrated items that measure a defined underlying trait such as QoL and becomes operational by the use of computer adaptive testing [37].*The Glau-QoL questionnaire:* The Glau-QoL is a comprehensive glaucoma-specific QoL instrument and has been validated in patients with glaucoma [38].*The AQoL-7D:* The AQoL-7D is a health-related multi-attribute utility instrument to assess QoL [39, 40]. This descriptive system comprises seven domains describing QoL (including vision) with levels of increasing severity. A scoring algorithm, based on general population values for health states defined by the descriptive system, is used to assign utilities to each health state (domain) described by the instrument and overall QoL. The AQoL-7D has been used in several RCTs in Australia and its overall and subscale measures have been found to be sensitive to interventions [41–44]. All QoL outcome measures will be interviewer-administered.

#### Clinical

Clinical secondary outcomes will be determined by the success rates of IOP reduction (defined as >25 % fall in IOP from baseline), changes in the visual field and optic disc from baseline to 24 months. The times required to reach these changes will be reported. Changes in the optic nerve head will be based on rim thinning, haemorrhage, or an increase in cup to disc (C/D) ratio and visual field changes based on progression.

### Statistical analysis plan

All data analyses will be conducted according to a pre-specified analytical plan using Stata version 12.1.0 (Stata Corp, College Station, TX). All hypothesis testing will be performed at the 5 % two-sided significance level. Analyses and data summaries will be carried out using the intention to treat (ITT) population. The ITT population is defined as all patients registered for active follow-up regardless of non-adherence with the intervention. All patients will be analysed according to the intervention that they were randomised to. A per-protocol analysis will be considered if there are a considerable number of protocol violators.

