### Specific aims

Aim 1: Our first aim is to compare the effect of SLT and topical medication on glaucoma-specific QoL at 6 weeks and at 6, 12, and 24 months post-treatment (primary outcome).

Aim 2: Our second aim is to quantify the cost-effectiveness of SLT treatment compared with glaucoma medication treatment.

Aim 3: Our third aim is to determine factors associated with treatment outcomes at 12 and 24 months post-SLT, including the rate of IOP success, defined as >25 % reduction in IOP from baseline measurements.

Aim 4: Our final aim is to assess the impact of SLT and eye drops on safety, laser-linked complications, and common side effects for glaucoma patients after the initiation of treatment.

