### Selective laser trabeculoplasty

For patients assigned to the SLT treatment arm, a single application of pilocarpine (1 %) and apraclonidine (1 %) or brimonidine (0.2 % or 0.15 %) will be instilled into the operative eye prior to the laser (Fig. 1). A frequency doubled, q-switched Nd:YAG laser emitting at 532 nm with a pulse duration of 3 ns, a spot size of 400 μm, and pulse energies ranging from 0.2 to 1.7 mJ, coupled to a slit lamp delivery system with a helium-neon laser aiming system will be used in all cases. Any mirrored gonioscopic lens that does not magnify is acceptable for use during the procedure. The laser will be focused on the trabecular meshwork using the HeNe aiming beams and a single laser pulse will be delivered at the 3 o’clock position. The laser energy will be increased or reduced by 0.1-mJ increments until fine ‘champagne’ bubbles are generated. During laser application, bubble formation will be monitored with each pulse to avoid excessive bubble formation and to avoid no observed response.

Initial 180° treatments of approximately 50 applications will be applied inferiorly from the 3 to 9 o’clock position. The total number of pulses delivered and the total amount of energy delivered will be recorded following each treatment. Participants will return for review of treatment response in 6 weeks from the baseline treatment and will then follow a stepped regimen, depending on their response to treatment. If a second SLT treatment is required, it will be applied over 180° from the 9 to 3 o’clock positions (superiorly). Treatment changes may also be initiated if there is an adverse event post-treatment and if this is considered severe enough to warrant a change in treatment.

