### Topical ocular hypotensive therapy

Patients randomised to the topical medication treatment group will be initially prescribed, where possible, a prostaglandin analogue with one drop to be instilled in each eye (or the study eye only if only one eye is enrolled) once daily (Fig. 2). We will instruct patients on how and when to instil their drops and stress the importance of adherence. Patients will return for review of treatment response 6 weeks from the baseline initiation of treatment and will follow a stepped regimen, depending on their response. We will change treatment if there is an adverse event that is considered severe enough to warrant such change or if there is progression in visual field loss or optic disc changes. Treatment response will be defined as follows:Successful response ≥25 % IOP reduction compared with baselines.Partial response = 10-25 % IOP reduction compared with baselines.No response = ≤10 % IOP reduction compared with baselines.

If patients have crossed over with both treatment regimens, they will exit the trial with further management at the discretion of the treating doctor (Figs. 1 and 2).

Based on the grading system developed by the Collaborative Initial Glaucoma Treatment Study (CIGTS) [35], optic discs will be clinically analysed for the following characteristics: (a) vertical and horizontal central cup to disc ratio; (b) focal and diffuse thinning of neuro-retinal rim; (c) presence of a disc haemorrhage; (d) nerve fibre layer defects; and (e) extent of peripapillary atrophy. If a change in treatment is deemed necessary and urgent, it may be initiated by the site investigator although the images would be reviewed by the Optic Disc Outcomes Committee (ODOC), masked to the treatment allocation (and initially the temporal sequence of the photos) to validate treatment change. For all disc changes considered non-urgent, these images will be referred to the ODOC where it will be the final arbiter on the presence/absence of optic disc changes and any alteration to treatment regimens. Visual field progression will be defined according to the following criteria identified by the Glaucoma Progression Alert on the Humphrey Visual Field result:Possible progression = 3 or more points show deterioration on at least 2 consecutive visits.Likely Progression = 3 or more points show deterioration on at least 3 consecutive visits.No progression detected = none of the above conditions is met.

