#### Clinical efficacy

To assess clinical efficacy (IOP reduction success), Chi square tests will be used and multivariable logistic regression models with odds ratios (OR) and 95 % CI will be built. Other analyses will be tailored to the nature of the secondary outcome data. Numerical data (for example, IOP and visual acuity) and dichotomous data (presence/absence) will be analysed by the GEE. Survival data (for example, time-to-VF (visual field) progression, IOP becoming uncontrolled again) will be analysed using survival analysis. Stepwise multiple regression analyses for secondary outcomes will evaluate a similar set of potential explanatory factors (covariates) in addition to treatment assignment and those evaluated for the primary analysis. Time-varying covariates will be used for analyses evaluating repeated measures of the outcome, if appropriate. Standard errors of estimates from log-linear models will take account of possible over-dispersion with respect to the assumed models.

To determine the impact of SLT (single or multiple applications) on safety, surgical complications, and common side effects associated with glaucoma treatment, Chi square tests will be used initially and regression models with ORs and 95 % CI will be built. Where appropriate, Poisson regression will be used to compare event rates (for example, adverse events). To determine the predictors of IOP reduction success, survival curves will be constructed using the Kaplan-Meier method. Cox proportional hazards method will be used to adjust for confounders. Hazard ratios (HR) with 95 % CI will be provided to estimate the relative risk.

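### Safety falls under the blanket rule of analysis by randomised arm although crossover is planned, which dilutes the per-treatment contrast that Aim 4 asks for; a table by treatment received should be added

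*Protocol article*

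**What the plan says.** The Statistical analysis plan section of the protocol article opens with a general rule: "Analyses and data summaries will be carried out using the intention to treat (ITT) population". It then fixes the grouping: "All patients will be analysed according to the intervention that they were randomised to". Neither sentence exempts safety. The only other population mentioned is conditional: "A per-protocol analysis will be considered if there are a considerable number of protocol violators".

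Crossover is part of the design. The section on topical therapy states: "If patients have crossed over with both treatment regimens, they will exit the trial". For the laser arm, the first response-driven step is dated: "Participants will return for review of treatment response in 6 weeks from the baseline treatment and will then follow a stepped regimen". The topical arm has the same 6-week review.

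The safety question is worded in terms of the treatments. Under Specific aims, Aim 4 reads: "Our final aim is to assess the impact of SLT and eye drops on safety, laser-linked complications, and common side effects". The safety paragraph under Clinical efficacy begins: "To determine the impact of SLT (single or multiple applications) on safety, surgical complications, and common side effects". It goes on to chi-square tests, regression models and, where appropriate, Poisson regression for event rates, but does not say which groups are compared.

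**The concern.** Aim 4 and the safety paragraph ask what each treatment does to patients, whereas the general rule answers what happens to patients allocated to each stepped regimen. The two questions separate once patients change treatment. A post-laser pressure spike in a drops-arm patient who has moved to laser would be counted in the drops column. Ocular surface disease that starts on drops in an SLT-arm patient who has moved to drops would be counted in the SLT column.

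The trial hypothesises fewer side effects and less frequent ocular surface disease with SLT. A table by arm alone would understate that contrast if it exists. It would also place some laser-linked events in the column a reader takes to be the non-laser group. For harms, shrinkage towards no difference is the less cautious direction.

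The per-protocol option does not fill the gap. A patient who crosses over as the regimen directs has not violated the protocol, and a per-protocol set is not grouped by treatment received.

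**Working it through.** **Figure in the plan.** The article states no event rate, crossover rate or power for safety, so there is no figure of its own to reproduce.

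**Inputs from the article.** Allocation 1:1; 193 enrolled per group; 15% attrition over 2 years, hence 193 × 0.85 = 164 per group with 24-month data; 5% two-sided tests; first response review at 6 weeks.

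**Assumed inputs (not in the article).** A drop-type side effect with risk 30% in patients exposed to drops and 10% in patients who are not. A fraction *c* of the SLT arm moves to drops, with *c* = 10%, 20% or 30%.

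**Model.** Every patient starts on the allocated treatment and keeps the risk from it. A patient who crosses over acquires the risk of the second treatment in full.

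- Drops arm: 30%.
- SLT arm: (1 − *c*) × 10% + *c* × 30% = 10% + 20% × *c*.
- By-arm difference: 20 points × (1 − *c*).

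| *c* | Drops arm | SLT arm | Difference | Power, 164 per arm | Power, 193 per arm |
|---|---|---|---|---|---|
| 0 | 30% | 10% | 20 points | above 99% | above 99% |
| 10% | 30% | 12% | 18 points | 98% | 99% |
| 20% | 30% | 14% | 16 points | 94% | 97% |
| 30% | 30% | 16% | 14 points | 86% | 91% |

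Power is for a two-proportion comparison. The 193 column may be the closer one for adverse events, since these are recorded throughout the 2 years and not only at 24 months.

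**Laser-type events.** The same factor (1 − *c*) applies, with *c* now the fraction of the drops arm that receives laser. With an assumed 15% risk after laser and none without, the difference falls from 15 points to 13.5, 12 and 10.5 points, and power at 193 per arm stays at 94% or more. Rarer events lose more: at an assumed 5% risk with no background, power at 193 per arm falls from about 88% to 77% at 10% crossover and 49% at 30%.

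**Direction of the approximation.** Giving crossed-over patients the full risk of the second treatment overstates dilution, because they are exposed to it for only part of the 2 years. The differences above are therefore lower limits, and the dilution an upper bound, for each crossover fraction. This assumes that first-treatment risk is kept in full and that patients who cross over have the same underlying risk as the rest.

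**Timing.** The article's Side-effects section defines pressure spikes within the first 4 weeks after treatment and records anterior chamber reaction 1 hour after laser. After the initial session both precede the 6-week review, so they stay in the SLT column. Only laser given after a later crossover produces laser events in the drops arm.

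**The case against.** The strongest reply is that by-arm reporting is not an error. The arms are stepped regimens with crossover built in, the trial asks which first-line strategy is better, and Aim 4 refers to effects after the initiation of treatment. For that question the randomised comparison of harms is valid and is the only one protected by randomisation. This stands. A reader might infer that Aim 4 is biased towards no difference; the documents support only dilution, and only when the target is the effect of each treatment itself.

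A reader might also infer that events are certain to be booked to the wrong treatment. The text does not go that far. The safety paragraph speaks of "To determine the impact of SLT (single or multiple applications) on safety, surgical complications, and common side effects associated with glaucoma treatment", and the number of applications is treatment received. Each adverse event is also graded for its relationship to study treatment. Attribution by exposure is therefore possible, and the general rule and the safety paragraph are best described as unreconciled. Grading single events does not, however, change the column in which they are counted.

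A larger effect can be computed by swapping risks completely at crossover: (1 − *c*) × own risk + *c* × other risk in each arm. This gives differences of 16, 12 and 8 points, with power of 96%, 78% and 44% at 164 per arm. It treats a crossed-over patient as never having had the allocated treatment, whereas both regimens start every patient on it. Those figures should not be used.

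Finally, a safety set is commonly defined in a full analysis plan, which is not shown, so its absence alone is no finding. That is right. The point rests on the rule that the article does state, without exception, for all analyses and summaries.

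**Conclusion.** The point holds as a modest one. The general rule, followed literally, answers a different question from the one posed by Aim 4 and the safety paragraph. The by-arm contrast is (1 − *c*) times the per-treatment contrast: 18 to 14 points instead of 20 for crossover of 10% to 30%, as an upper bound on dilution. The rates are assumptions and the true size cannot be known from the article. Frequent side effects would still be detected with good power; rare harms are more exposed. Complications of the initial laser session are little affected, so the documents do not support a claim that laser harms would be hidden in general. Nor is there a case for replacing the randomised-arm table: it is valid for comparing strategies and should stay.

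**What to change.** 1. Keep the safety table by randomised arm.
2. Qualify the general rule in the Statistical analysis plan section, so that safety is summarised by randomised arm and also by treatment received.
3. In the safety paragraph under Clinical efficacy, name the groups to be compared.
4. Add a descriptive table by treatment received at event onset: laser-linked events per SLT session, in whichever arm the session was given; drop side effects and ocular surface disease by time on drops.

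The cost is a few sentences and one extra set of tables. Adverse events are already recorded throughout the 2 years, and pulses and energy are recorded for each laser treatment; start and stop dates of drops are also needed, and the article does not say whether they are collected. The downside is that the added table is not randomised. Treatment changes follow poor response, adverse events or progression, so the groups are selected. The table should be labelled descriptive and read beside the by-arm table.

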#### Baseline characteristics

Analyses will be performed for all variables at baseline to detect potential bias in recruitment. Continuous variables will be reported using means ± standard deviations (SD) or median (interquartile range (IQR)). For dichotomous/categorical variables, absolute numbers and percentages will be computed, together with their 95 % confidence intervals (CI). The comparison of means will be carried out using Student’s t test, the Mann-Whitney test, analysis of variance or the Kruskall-Wallis test as appropriate. The difference in proportions between the two treatment groups will be carried out using Chi-square statistics. These comparisons will be made by assessing the prognostic relevance of the difference observed, not through hypothesis testing. Baseline summaries with respect to the main covariates will be presented and discussed from a clinical point of view, irrespective of whether a statistical test indicated a ‘statistically significant difference’ between treatment groups. If we find a strong baseline imbalance in a variable, we will include this variable as a covariate in a sensitivity analysis to allow assessment of the robustness of the conclusions drawn from the primary analysis.

#### Primary analysis

The primary analysis will be ITT analysis, which includes all randomised patients in the groups to which they were randomly assigned, regardless of their adherence with the entry criteria, the treatment they actually received, and of subsequent withdrawal from treatment or deviation from the protocol. The ITT analysis will include all patients with 24-month GOAT, Glau-QoL, and AQoL-7D data. The GOAT will be our main primary outcome. The GOAT and Glau-QoL data will initially undergo Rasch Analysis (a form of Item Response Theory - IRT) using Winsteps software (version 3.90), Chicago, Illinois [45].

We will examine the missing data mechanism (probability distribution of missingness) to determine whether it is missing completely at random (MCAR), missing at random (MCR) or missing not at random (NMAR). Since patient-centred measurements will recur on the same patients, longitudinal HRQoL data will be analysed using multivariate generalised estimating equation (GEE) or generalized linear mixed models (GLMMs). We will adjust for pre-defined variables that we consider are associated with the primary outcome (HRQoL) from the literature. These include clinical variables (for example, baseline glaucoma severity, visual field, visual acuity, optic disc changes, duration of glaucoma), and sociodemographic variables (for example, age, gender). Separate regressions will be conducted for each QoL parameter. These models take into account the correlation within observations on the same subject and allow for inclusion of data on subjects who have only partial follow-up without imputing missing data. To handle multiplicity in the multiple regression models, Bonferroni adjustment will be used.

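### The primary analysis set is defined inconsistently, and one of the defining sentences reads as a 24-month completer set rather than intention to treat

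*Protocol article*

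**What the plan says.** In the Primary analysis section of the protocol article, the primary analysis is an ITT analysis "which includes all randomised patients in the groups to which they were randomly assigned", regardless of adherence to entry criteria, of treatment received "and of subsequent withdrawal from treatment or deviation from the protocol". The next sentence reads: "The ITT analysis will include all patients with 24-month GOAT, Glau-QoL, and AQoL-7D data". The second paragraph of that section plans GEE or generalised linear mixed models, with a separate regression for each quality-of-life parameter, and supports them on the ground that they "allow for inclusion of data on subjects who have only partial follow-up without imputing missing data".

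The Statistical analysis plan section words the population differently: "The ITT population is defined as all patients registered for active follow-up regardless of non-adherence with the intervention". It adds that patients are analysed in the arm to which they were randomised.

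The section on topical therapy contains the exit rule: "If patients have crossed over with both treatment regimens, they will exit the trial with further management at the discretion of the treating doctor". Movement through the stepped regimens depends on intraocular pressure (IOP) response at review. Treatment may also be changed for adverse events (both arms' sections) and for visual field or disc progression (topical therapy section). The article does not say whether questionnaires continue after exit.

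**The concern.** An ITT set is fixed at randomisation. A set defined by having 24-month questionnaire data is fixed by what happened over the following two years. If the 24-month sentence governs, a patient with data at 6 weeks, 6 months and 12 months but none at 24 months contributes nothing, although the chosen models are recommended because they can use exactly such a patient.

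The exit rule makes this more than a matter of wording. Exit follows from treatment changes, and those follow from response, adverse events or progression. If outcome collection stops at exit, patients who exit before 24 months have no 24-month data, and a completer set then excludes them for reasons linked to how treatment went. The two arms follow different stepped regimens, so equal exit cannot be taken for granted.

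The model choice is affected too. Unweighted GEE is valid in general only if data are missing completely at random. A likelihood-based mixed model needs only missing at random, given the observed data that it models. Exit driven by observed response fails the stricter condition. The plan to examine the missingness mechanism does not settle this, because observed data cannot separate missing at random from missing not at random.

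**Working it through.** **The statements side by side**

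- A, Primary analysis, opening sentence: all randomised patients, as assigned, whatever happens later.
- B, Primary analysis, next sentence: patients with 24-month data on the named instruments.
- C, Statistical analysis plan: patients registered for active follow-up, as randomised.
- D, Primary analysis, second paragraph: the models take in patients with partial follow-up.

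A and D agree. C is loose but can be read as everyone enrolled, which agrees with A. B agrees with A only if it restricts nothing, in which case it adds nothing. Its natural reading is a restriction, and that contradicts A and D.

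**Reproducing the planned sample size**

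Inputs from Sample size estimation and Statistical analysis plan: effect size 0.3, two-sided 5 %, 80 % power, 15 % attrition, 193 enrolled per group.

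- n per group = 2(1.960 + 0.842)² / 0.3² = 174.4, so 175. The t-test version gives 175.4, so 176. Both stated figures reproduce.
- Patients expected with 24-month data: 193 × 0.85 = 164 per group, a loss of 29.
- Power with 164: Φ(0.3 × √(164/2) − 1.960) = 77.5 %.
- Enrolment needed to keep 175 or 176 after 15 % loss: 175/0.85 = 206 or 176/0.85 = 208, not 193.

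The drop from 80 % to 77.5 % therefore comes from the enrolment figure not matching the stated attrition. That is a separate error and is not caused by the analysis-set wording.

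**What sentence B could add in lost power (assumption)**

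Suppose a further 5 %, 10 % or 15 % of the 164 are excluded through exit or a missing instrument. These rates are not in the article. The numbers left are 156, 148 and 139 per group, with power of 75.4 %, 73.2 % and 70.7 %.

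**What sentence B could add in bias (assumption)**

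Let a share e₁ exit in one arm and e₀ in the other, let those who exit be g SD worse than those who stay, and let the true all-randomised difference be zero. The mean of those who stay lies g × e above the arm's full mean, so the completer difference is g × (e₁ − e₀).

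- 5 % vs 5 %, any g: 0.
- 5 % vs 10 %: 0.3 × 0.05 = 0.015 SD, up to 0.8 × 0.05 = 0.04 SD.
- 5 % vs 15 %: 0.3 × 0.10 = 0.03 SD, up to 0.8 × 0.10 = 0.08 SD.

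As a share of the 0.3 SD target, the non-zero values run from 0.015/0.3 = 5 % to 0.08/0.3 = 27 %. The implied SD is 0.156/0.3 = 0.52 logit, so the range is 0.008 to 0.042 logit. The arm with more exits looks better than it is.

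**The case against.** The strongest reply is that the article does not establish a completer analysis. Sentence B does not contain the word only. The sentence before it keeps patients who withdraw from treatment, and the modelling paragraph uses partial follow-up. Two statements favour full inclusion and one favours completers. This stands: what can be shown is an unresolved contradiction.

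Several stronger readings are tempting and are not supported.

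- A reader might infer that a patient lacking one of the three questionnaires is discarded. Because each quality-of-life parameter has its own regression, the 24-month condition may apply instrument by instrument.
- A reader might infer three irreconcilable ITT sets. The phrase about active follow-up can mean enrolled, and it sits beside analysis as randomised. Only the 24-month sentence clearly conflicts.
- A reader might equate exit with two treatment failures. The text speaks of crossing over with both regimens, treatment may also change for adverse events, and the pathway figures are not available here.
- A reader might charge the 29 patients lost per arm to this rule. They are the protocol's own assumed attrition and would lack 24-month data under any analysis set.
- A reader might infer that exited patients also leave the IOP denominator. Nothing in the article says so.

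It can also be said that choosing between GEE and a mixed model, and adding a sensitivity analysis, commonly belongs to a statistical analysis plan. Taken alone, that is fair. Here the two are needed to make a corrected population statement work. What the objection does not remove is that sentence B, followed as written, gives a set that is not ITT, and that an analyst could defend either set after seeing the data.

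**Conclusion.** The concern holds as an inconsistency in who enters the primary comparison. One sentence naturally reads as a completer restriction, contradicts its neighbours and, if applied, would exclude patients on a post-randomisation condition. Combined with the exit rule, and with no stated outcome collection after exit, that exclusion can depend on treatment response.

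Its size and direction are not determinable from the article, because no exit rates by arm are given. The 0.015 to 0.08 SD range rests on assumed exit gaps of 5 to 10 points and an assumed deficit of 0.3 to 0.8 SD, and the bias is zero if exit is equal. The contradiction itself is certain. That the final analysis will be a selected completer analysis is an inference that the article does not support.

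**What to change.** Four changes are needed.

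1. In Primary analysis, delete the sentence that ties the ITT analysis to 24-month data. In Statistical analysis plan, replace the phrase about active follow-up so that both sections define one set: all randomised patients in their assigned arm.
2. Name a likelihood-based mixed model using every available visit as the primary model, with the between-arm difference at 24 months as the contrast. Do not leave unweighted GEE as an equal alternative.
3. Beside the exit rule, state that leaving the stepped regimen does not end the planned questionnaires and IOP measurements, which continue to 24 months. Clinical management stays as written.
4. Add one missing-not-at-random sensitivity analysis in which patients who stop providing data are given worse outcomes, over a range fixed in advance.

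The cost is wording in three sections, a little more analysis work, and completion of already scheduled assessments in patients who exit the regimens. The third change is the most pressing, because 24-month data that were not collected cannot be recovered later. The mismatch between 193 enrolled and 15 % attrition needs its own correction.
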